#### Relevant concomitant care permitted or prohibited during the trial {11d}

Organisations in the control arm must agree not to adopt MHFA training until after the study period.

#### Provisions for post-trial care {30}

Participants will be debriefed and provided with a written report of the outcomes containing contact details of the research group should they require further information.

### Outcomes {12}

#### Primary outcome

The primary outcome is Employees’ help-seeking behaviour at 6 months measured by the Actual Help-Seeking Questionnaire [AHSQ] [11]. The AHSQ measures help-seeking behaviour in the 2 weeks preceding the assessment and will be assessed at baseline, 6, 12 and 24 months. Help-seeking behaviour is determined by listing the number of help sources, the type of help sought and whether help seeking has occurred during the allocated time period.

The primary analysis will be conducted on those participants who receive MHFA and therefore is a per protocol analysis. Further analyses will examine the impact of the intervention at the organisational level using an intention-to-treat analysis with all respondents included.

As this is a small non-random subsample of randomised participants, it is recognised that this analysis will be vulnerable to selection bias and uncontrolled confounding. For this reason, a range of baseline participant characteristics will be included in the primary analysis to mitigate these limitations.

#### Secondary outcomes

All secondary outcomes and their measures are described in Table 1. In addition to these outcome measures, the researchers will also capture data on organisations’ sickness absence levels, presenteeism rates and measures of productivity.

**Table 1 Tab1:** Data collection schedule and secondary outcome measures

Measure	Timing of measures				
	Baseline	Post-intervention (up to 3 months)	6 months	12 months	24 months
Demographics (age, gender, level of education, ethnicity, nature and frequency of and MHFA interventions directly experienced, etc.)	X				
Employees help-seeking intentions (General Help-Seeking Questionnaire) [12]	X	X	X	X	X
Employees’ mental health and wellbeing (Warwick-Edinburgh Mental health and Well-being Scale) [13]	X	X	X	X	X
Mental health first aiders’ mental health literacy (Mental Health Literacy Scale) [14]^a^	X	X	X	X	X
Mental health first aiders’ skills (ALGEE scoring system) [15]^a^	X	X	X	X	X
Employees’ quality of life (EQ-5D-5L and Short Form-12 Health Survey SF-12) [16]	X	X	X	X	X
Employees’ self-efficacy (Self-Efficacy for Seeking Mental Health Care Scale) [17, 18]	X	X	X	X	X
Employees’ social well-being (Social Well-being Scale) [19]	X	X	X	X	X
Employees’ use of standard mental health and other services (adapted version of the Client Services receipt Inventory) [20]	X	X	X	X	X

^a^Intervention group

### Assessment of cost-effectiveness

This component will answer the research question ‘Is MHFA more cost-effective than usual practice?’ This requires comprehensive estimates of the financial benefits derived from MHFA and its costs. Consequently, the evaluation will analyse the data from three perspectives reflecting the three main groups impacted by MHFA:
Personal (employees’ quality of life)State/government (use of health and social services)Employers (staff productivity)

Data will be combined with unit cost data to provide a financial estimate of the change in service use observed. The results for those who had the MHFA training and those who did not will determine whether it is more cost-effective to purchase the training or not.

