### Trial design {8}

The study is a multi-centred two-arm cluster RCT comparing organisations implementing MHFA (intervention arm) with a consultation on mental health and wellbeing in the workplace (control arm).

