### Interventions

#### Explanation for the choice of comparators {6b}

The control arm is termed as usual practice and is defined as an organisation that has not previously introduced MHFA and agrees to not introduce the 2-day MHFA training during the period of the study. The organisations allocated to usual practice arm will receive a brief consultation from MHFAE on the promotion of mental health and wellbeing in the workplace.

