#### Intervention description {11a}

The MHFA intervention has three parts:
The 2-day MHFA training provided by MHFAE. This is a manualised training programme designed to provide individuals with the following: an in-depth understanding of mental health and the factors that can affect wellbeing, practical skills to spot the triggers and signs of mental health issues, confidence to step in, reassure and support a person in distress, enhanced interpersonal skills such as non-judgemental listening, knowledge to help someone recover their health by guiding them to further support—whether that is self-help resources, through their employer, the NHS, or a combination.Raising awareness of the presence of MHFA in the organisation.The application of MHFA to participants in the workplace. The MHFA training uses a manualised five-stage approach, ALGEE: Approach the person, assess and assist with any crisis; Listen and communicate non-judgementally; Give support and information; Encourage the person to get appropriate professional help and Encourage them to seek other forms of support.

MHFAE recommend training one employee in MHFA per ten employees; however, organisations are free to ask for any number of employees to be trained. The current study will record the ratio of participants trained in each organisation. No stipulation is made as to the selection of participants to be trained, and organisations are encouraged to advertise the training to all staff. The selection criteria used by each organisation will be assessed in the qualitative component of this study.

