**Assignment of interventions: allocation**

**Sequence generation {16a}**

**Concealment mechanism {16b}**

**Implementation {16c}**

#### Randomisation

The unit of randomisation is organisation, and randomisation of organisations will be stratified by size of organisation, with three strata being defined [22], small (< 50 employees), medium (50–249 employees) and large (> 250 employees). The randomisation schedule will be generated by GD using Random.org (https://www.random.org/randomness/) and allocation assigned to an organisation after completion of baseline measures.

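### The deciding cost-effectiveness contrast is set by who had MHFA training, not by randomised arm, and so does not match the section's own question

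*Protocol article*

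**What the plan says.** The section Assessment of cost-effectiveness opens with its aim: "This component will answer the research question ‘Is MHFA more cost-effective than usual practice". Under Explanation for the choice of comparators {6b}, that comparator is tied to the arm and to organisations: "The control arm is termed as usual practice and is defined as an organisation that has not previously introduced MHFA". The Randomisation section agrees: "The unit of randomisation is organisation". Trial design {8} describes the same two-arm comparison of organisations.

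The sentence that settles the economic question is worded differently: "The results for those who had the MHFA training and those who did not will determine whether it is more cost-effective" to buy the training.

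Intervention description {11a} lists three parts to the intervention: the two-day course, making staff aware that MHFA is available, and trained staff using it with colleagues. Training is meant for a minority: "MHFAE recommend training one employee in MHFA per ten employees". Organisations may choose another number, and the protocol does not prescribe who is trained.

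Under Outcomes {12}, the primary analysis is per protocol, in participants who receive MHFA. An intention-to-treat analysis is added there as a further analysis. Neither statement is extended to the economic evaluation.

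**The concern.** Having had the training is neither the randomised allocation nor the receipt of help from a first aider. Trainees are chosen by themselves or by their employer, so a contrast between trainees and everyone else loses the protection of randomisation. It also puts untrained colleagues in MHFA organisations, whom the intervention is meant to reach, into the comparator.

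The benefits that the section names are employees' quality of life, use of services and staff productivity. Much of any such benefit would arise in untrained colleagues. Cost-effectiveness is a stated objective of the trial, and an employer's choice is whether to bring MHFA into the organisation. The contrast between arms answers that; the contrast between trained and untrained people does not.

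**Working it through.** **Inputs.** The Sample size section gives 400 participants per condition. The trained share of respondents, r, is an assumption: 0.10 follows the recommended ratio, and 0.05 to 0.30 is shown because organisations choose the number.

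**The plan's own figure.** The cost-effectiveness section gives no number, so the check is on the 400 per arm. For a difference of 2, SD 8, two-sided alpha 0.05 (two-sided is assumed) and 80% power, the t-test calculation gives 252.1, so 253 per arm and 506 in all. Attrition: 506/0.85 = 595.3, so 596. Design effect: 1 + (29 − 1) × 0.01 = 1.28, and 596 × 1.28 = 762.9, so 763, which the plan rounds to 800. The figures reproduce and are not affected by this point.

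**Make-up of the literal contrast at r = 0.10.**
- Trained: 400 × 0.10 = 40.
- Untrained in MHFA organisations: 400 − 40 = 360.
- Everyone untrained: 400 + 360 = 760.
- Share of the comparator working in MHFA organisations: 360/760 = 0.474.

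With equal arms the share is (1 − r)/(2 − r), so it does not depend on the total sample size.

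**Effect on an equal benefit.** Suppose every employee of an MHFA organisation gains d and controls gain nothing. The trained mean is d and the untrained mean is 0.474d. The contrast is d − 0.474d = 0.526d, or in general d/(2 − r).

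**Precision.** With a common SD and clustering ignored, the standard error relative to 400 v 400 is √(1/40 + 1/760) / √(2/400) = 0.1622/0.0707 = 2.29.

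| Trained share (assumed) | Trained v untrained | Comparator in MHFA organisations | Equal benefit retained | SE ratio to 400 v 400 |
|---|---|---|---|---|
| 5% | 20 v 780 | 49% | 0.51 | 3.20 |
| 10% | 40 v 760 | 47% | 0.53 | 2.29 |
| 20% | 80 v 720 | 44% | 0.56 | 1.67 |
| 30% | 120 v 680 | 41% | 0.59 | 1.40 |

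By randomised arm the comparison is 400 v 400, with nobody from an MHFA organisation in the comparator.

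**When the sign would change.** If trainees gain k·d and untrained colleagues gain d, the contrast at r = 0.10 is (k − 0.474)d. It is negative only if k is below about 0.47; at k = 0 it is −0.47d.

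These figures leave out selection of trainees, which could bias the contrast in either direction.

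**The case against.** The strongest reply is that the sentence means organisations. It says 'those', not 'people'. It ends on a decision to purchase, and organisations are the ones that ask for training. The eligibility and concomitant-care sections speak of organisations undertaking or adopting the training, and the exclusion criteria use 'those' for organisations. Sickness absence, presenteeism and productivity are described as organisations' data, which do not readily split by individual. Quality of life and service use are collected from employees generally. On this reading the sentence is loose wording for the two arms.

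Much of that stands: the organisational reading is tenable, and the wording does not establish that individuals are meant. It does not remove the point, for two reasons. First, the intervention section also speaks of participants being trained, and the protocol does choose a person-level contrast by receipt for its primary analysis. An analyst could therefore follow the sentence literally. Second, even for organisations, having had the training is not allocation. An organisation allocated to MHFA that never trained anyone would change sides.

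Three stronger inferences are not supported:
- **The result would point the wrong way.** That needs trainees to gain less than about half of what their colleagues gain, which the protocol does not suggest. Equal benefit gives attenuation without reversal.
- **Training cost would fall on trainees alone, at about ten times the arm-wide cost per head.** No section says how that cost is apportioned, and an article may leave this to the full plan.
- **Calling the comparator usual practice conceals the consultation.** The comparator section discloses it openly: "The organisations allocated to usual practice arm will receive a brief consultation from MHFAE". Nothing says that its cost will be left out.

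**Conclusion.** The concern holds as a mismatch in the text. The sentence that decides cost-effectiveness names a contrast by receipt of training, while the section's question, the definition of the comparator and the unit of randomisation all call for a contrast by arm.

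The size is conditional. The 47% share and the retained 0.53 of an equal benefit hold only if the sentence is read at the level of individuals, with equal arms and 1 in 10 respondents trained. Over 5% to 30% trained, the share runs from 49% to 41% and the retained benefit from 0.51 to 0.59. They describe the benefit side only, since the article gives no costs. On the organisational reading the remaining fault is smaller: grouping by what was done instead of by what was allocated. The documents do not show which reading was intended, so the wording needs correcting; it is not proof that a biased analysis is planned.

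**What to change.** Replace the deciding sentence with a statement that costs and outcomes will be compared between the randomised arms. All participating employees of organisations allocated to MHFA should count in the intervention arm, whether or not they or their organisation were trained, and the analysis should allow for clustering by organisation. Any comparison of trained with untrained staff should be labelled exploratory.

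This is a change of wording. It needs no new data, because Table 1 already collects quality of life and service use from employees generally, and allocation is known for every organisation. The sample size does not change. The cost is a protocol amendment through the route that the article describes, including ethics committee approval, with matching text in the health-economics plan.

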### Participant timeline {13}

#### Sample size {14}

The sample size calculation is based on a simplification of the proposed analysis model (Fig. 1).

**Fig. 1 Fig1:**
[figure not shown]
CONSORT trial flow diagram

To be able to detect a change of two additional help seeking resources [11], with 80% power at the 0.05 alpha level, assuming that the mean in the control group is 1 and in the intervention group 3 with a common standard deviation of 8, 506 participants are required, increasing to 596 allowing for 15% attrition at 6 months. Pilot data indicates a response rate of 40% across organisations and an average cluster size of 72 employees (calculated from organisations currently signed up) therefore approximately 29 employees per organisation (cluster size). With 24 clusters, 12 organisations per condition, and assuming an intraclass correlation coefficient (ICC) equal to 0.01 (ICC’s are lower for participant outcomes as opposed to process variables, when cluster size is large and when estimates are adjusted by participant baseline characteristics [21]), a minimum target sample size is 763, rounded up to 800, 400 per condition

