### Statistical methods

#### Statistical methods for primary and secondary outcomes {20a}

All outcomes will be described with the appropriate descriptive statistics: mean and standard deviation for continuous outcomes (or medians and interquartile range for skewed data) and counts and percentages for dichotomous and categorical outcomes.

The analysis of the primary outcome will estimate the mean difference (with 95% confidence intervals) in the Actual Help-Seeking score at 6-month follow-up between the intervention (MHFA) and standard care groups using a mixed effects repeated measures model (which assumes incomplete outcome data to be missing at random). The model will incorporate demographic and other baseline covariates as fixed effects. The dependent variable will be the count of help sources on the Actual Help-Seeking questionnaire. The independent variable will be ‘time point’. The effect size of the intervention will be estimated as the exponentiated coefficient for the interaction term between time point (baseline versus 6-month follow-up) and intervention status (MHFA versus control group). A random effect of participant will be included in the model to adjust for the repeated measures on participants. ‘Employing organisation’ will be included as a higher level random effect (with participants nested in employers). Statistical significance will be at the 5% level.

Secondary outcomes will be analysed using an appropriate generalised linear model, for example binary logistic regression for dichotomous outcomes and ordinal logistic regression for ordered categorical outcomes. All models will be adjusted for employing organisation and baseline score (where applicable).

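### The sample size rests on an unsourced SD of 8, which a count of help sources with mean 1 cannot have unless at least 65 sources can be counted

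*Protocol article*

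**What the plan says.** Protocol article, Sample size {14}: the target is two additional help sources, at a power of 80% and an alpha of 0.05. The inputs behind it are given in these words: "assuming that the mean in the control group is 1 and in the intervention group 3 with a common standard deviation of 8". The result is that "506 participants are required, increasing to 596 allowing for 15% attrition at 6 months". A cluster size of about 29 and an ICC of 0.01 then raise this to 763, rounded up to 800 (400 per condition). A reference is cited for the two-source change and another for the ICC. None is given for the SD.

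The outcome is fixed elsewhere in the article. Statistical methods {20a}: "The dependent variable will be the count of help sources on the Actual Help-Seeking questionnaire". Outcomes {12}: "The AHSQ measures help-seeking behaviour in the 2 weeks preceding the assessment". The number of sources that the questionnaire can count is not stated.

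The Abstract and Outcomes {12} place the primary analysis on participants who receive MHFA. Outcomes {12} calls them a small, non-random subsample. An intention-to-treat analysis of all respondents follows as a further analysis.

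**The concern.** A count of sources on a questionnaire cannot be negative and cannot exceed the number of sources that can be named. A mean of 1 with an SD of 8 is therefore suspect on its face. The SD is the input that turns a difference of two sources into 506 participants, and the attrition and clustering steps both start from that figure. If the SD is unattainable, the statement of 80% power for two extra sources does not describe this design. Readers of the results would then have the wrong benchmark for what the trial could detect.

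**Working it through.** **Inputs.** Means 1 and 3, SD 8, power 80%, alpha 0.05, attrition 15%, cluster size 29, ICC 0.01 and the target of 800 all come from Sample size {14}. Whether the test is one- or two-sided is not stated. The scale of the outcome comes from Outcomes {12} and Statistical methods {20a}. The maximum M, every SD other than 8, and the recipient fractions in step 5 are assumptions.

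**Step 1: reproduce the plan's figures.**
- Standardised difference: 2/8 = 0.25.
- Normal approximation, two-sided: n per arm = 2 × (1.960 + 0.842)² × (8/2)² = 251.2, so 252. The two-sample t calculation gives 252.13, so 253 per arm and 506 in total. A one-sided test would give 396 in total and does not match.
- Attrition: 506/0.85 = 595.3, so 596.
- Design effect: 1 + (29 − 1) × 0.01 = 1.28, and 596 × 1.28 = 762.9, so 763.

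All three figures match.

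**Step 2: the largest SD that a bounded count can have.** If 0 ≤ X ≤ M then X² ≤ MX, so E(X²) ≤ Mm and Var(X) ≤ Mm − m² = m(M − m). This holds for every distribution. Setting the variance to 8² = 64 gives M ≥ m + 64/m.
- Mean 1: M ≥ 1 + 64 = 65.
- Mean 3: M ≥ 3 + 21.3 = 24.3, so 25.

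Because the SD is common to both arms, the control arm sets the limit. Even at M = 65, an SD of 8 is reached only if 1 employee in 65 used all 65 sources within two weeks and everyone else used none.

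**Step 3: SD ceilings for assumed list lengths,** √(m(M − m)):

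| M (assumed) | mean 1 | mean 3 |
|---|---|---|
| 10 | 3.0 | 4.6 |
| 15 | 3.7 | 6.0 |
| 20 | 4.4 | 7.1 |
| 25 | 4.9 | 8.1 |

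**Step 4: what 800 detects if all are analysed.** Effective n per arm = 800 × 0.85/1.28/2 = 265.6. Detectable difference at 80% power = 2.802 × SD × √(2/265.6) = 0.243 × SD.
- SD 2: 0.49 sources. SD 3: 0.73. SD 5: 1.22. SD 8: 1.94.
- At the ceilings, averaging the two arms' variances: M = 10 gives (9 + 21)/2 = 15, SD 3.87, detectable 0.94. M = 20 gives (19 + 51)/2 = 35, SD 5.92, detectable 1.44.

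Power for a difference of two is above 99% for any SD up to 5, about 97% at the M = 20 ceilings, and 82% at SD 8.

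**Step 5: the recipient-based primary analysis.** The number of recipients is not given. For illustration, take 10% to 20% of 400 as recipients with 15% loss, compare them with all controls, and ignore clustering. That is 400 × 0.10 × 0.85 = 34 to 400 × 0.20 × 0.85 = 68 recipients, against 400 × 0.85 = 340 controls. Power for a difference of two is Φ(2/SE − 1.96), with SE² = v₁/n₁ + v₀/n₀.
- SD 3 in both arms, 34 recipients: SE² = 9/34 + 9/340 = 0.291, power about 96%.
- M = 10 ceilings: SE² = 21/34 + 9/340 = 0.644, power about 70%; with 68 recipients, about 93%.
- M = 20 ceilings: SE² = 51/34 + 19/340 = 1.556, power about 36%; with 68 recipients, about 61%.

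The answer runs from poor to ample depending on the SD, and the SD is the input that has no support.

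**The case against.** **The list length is not in the documents.** This stands: the impossibility is conditional on fewer than 65 countable sources. If the arms were allowed different SDs, their average variance could reach 64 when (M − 1 + 3(M − 3))/2 = 64, that is M = 34.5, so 35 sources with all-or-none responses in both arms. The protocol specifies a common SD, however, so 65 is the relevant figure.

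**Help-seeking counts are skewed with many zeros.** True, but the bound holds whatever the shape. An unbounded negative binomial could reach mean 1 and SD 8, with dispersion k = 1/(64 − 1) = 0.016 and about 94% zeros. A count of sources on a questionnaire is not unbounded.

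**The calculation is described as a simplification of the analysis model.** That can excuse a two-sample comparison of means. It does not excuse an SD that the variable cannot have.

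**Too large an SD is conservative.** This stands for the all-respondent comparison. A trial that may find a difference smaller than its target significant is not thereby invalid, and the protocol reports an estimate with a 95% confidence interval.

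**Stronger readings that the documents do not support.**
- A reader might infer that the trial is far larger than it needs to be. That treats all 800 as the primary analysis set, whereas the primary analysis is on recipients. Step 5 shows that power there could fall below 80%.
- A reader might infer that an average gain of two across all employees implies an implausible gain per recipient. The sample size section does not say that the two sources are an employee-wide average, no recipient fraction is given, and the intervention also includes raising awareness across the organisation.
- A reader might call this an arithmetic error. It is not: every step reproduces, and the fault lies in an input.

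**Conclusion.** The common SD of 8 is unsourced and is incompatible with a count of mean 1 unless at least 65 sources can be counted. What the calculation delivers is a trial sized for a standardised difference of 0.25. The label of two extra sources at 80% power fits only if the SD really is 8.

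If all 800 are analysed, with the protocol's own attrition, cluster size and ICC, the detectable difference is about 0.24 SD. That is roughly 0.5 to 1.2 sources for SDs of 2 to 5, and 0.9 to 1.4 at the ceilings for 10 to 20 sources. These SDs and list lengths are assumptions. The conclusion about the SD of 8 does not depend on them; it holds for every list shorter than 65.

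For the all-respondent intention-to-treat comparison the error is conservative. For the per-protocol primary analysis, the stated inputs do not allow power to be judged in either direction.

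**What to change.** Keep N and rewrite the sample size paragraph.

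1. State how many sources the questionnaire can count, and replace the SD of 8 with a sourced value. Use the pilot if it recorded the AHSQ; the article cites pilot data only for the response rate. Otherwise use the pooled baseline AHSQ variance. Randomisation places allocation after baseline measures, so these data need no unblinding. Baseline data speak to the mean before intervention, so say what variance is assumed at the higher mean.
2. Restate the detectable difference in mean sources and as a ratio, since Statistical methods {20a} reports an exponentiated coefficient.
3. Do this separately for the recipient-based primary analysis, with an expected number of recipients, and for the all-respondent intention-to-treat analysis.

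Cost: one paragraph and a short calculation, with no extra enrolment. The downside is that the published target and power figures will change.

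### Twenty-four organisations at about 29 respondents each give 696 employees, not the stated 763 or 800, and power of about 77% rather than 80% on the plan's own assumptions

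*Protocol article*

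**What the plan says.** All the figures stand in one paragraph of the protocol article, under Sample size {14} (printed after the Fig. 1 caption).

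- Target effect: "assuming that the mean in the control group is 1 and in the intervention group 3 with a common standard deviation of 8", "with 80% power at the 0.05 alpha level".
- Individual-level size and attrition: "506 participants are required, increasing to 596 allowing for 15% attrition at 6 months".
- Yield per organisation: a pilot response rate of 40% is applied to an average of 72 employees, "therefore approximately 29 employees per organisation (cluster size").
- Clusters: "With 24 clusters, 12 organisations per condition, and assuming an intraclass correlation coefficient (ICC) equal to 0.01".
- Result: "a minimum target sample size is 763, rounded up to 800, 400 per condition".

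Under Randomisation, the article adds that "randomisation of organisations will be stratified by size of organisation", in three bands from below 50 to above 250 employees. The introduction to the sample size section calls the calculation a simplification of the analysis model.

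**The concern.** The paragraph fixes three quantities that are tied by multiplication: the number of organisations, the respondents per organisation, and the total. Any two determine the third, and the three given do not fit together. The 29 is not a passing remark: it is the cluster size in the design effect that turns 596 into 763. The paragraph therefore uses 29 to say how many people are needed, and the same 29 with 24 organisations cannot supply them.

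If organisations are recruited to the stated count and respond at the stated rate, the trial ends below its own minimum and below its stated power. The number of organisations is a recruitment decision, so a later analysis plan cannot repair it. The article reports recruitment as open until January 2021.

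**Working it through.** **Inputs**, all from Sample size {14}: difference 3 − 1 = 2; SD 8; power 80%; alpha 0.05 (sidedness not stated; two-sided reproduces the plan's figure); attrition 15%; response 40% of 72; 24 organisations; ICC 0.01.

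**1. Reproducing the plan's figures.**
- Standardised effect 2/8 = 0.25. A two-sided t-test needs 252.1 per arm, rounded to 253, total 506. This agrees.
- Attrition: 506/0.85 = 595.3, rounded to 596. This agrees.
- Respondents per organisation: 0.40 × 72 = 28.8, about 29. This agrees.
- Design effect: 1 + (29 − 1) × 0.01 = 1.28. Then 596 × 1.28 = 762.9, rounded to 763. This agrees.

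**2. What the stated clusters supply.**
- 24 × 29 = 696 (691 with 28.8).
- 763 − 696 = 67, and 67/763 = 9%.
- 800 − 696 = 104, and 104/800 = 13%.

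**3. Power at 696 on the plan's method.** Effective n = 696 × 0.85 / design effect. Power = Φ(2 / (8 × √(4/effective n)) − 1.96).

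| Design effect | Effective n | Power |
|---|---|---|
| 1.28 (cluster size 29, as in the plan) | 591.6/1.28 = 462 | Φ(2.687 − 1.96) = 76.6% |
| 1.2365 (29 × 0.85 = 24.65 after attrition) | 591.6/1.2365 = 478 | Φ(2.734 − 1.96) = 78.1% |

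The plan requires an effective 506.

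**4. What would make the figures agree.**
- At 29 per organisation, 763/29 = 26.3, so 27 organisations, or 28 for equal arms. 800/29 = 27.6, so 28 organisations, giving 28 × 29 = 812. Effective n is 812 × 0.85/1.28 = 539 and power 82.7%.
- At 24 organisations, 800/24 = 33.3 each, and 33.3/72 = 46% response. Design effect is 1 + 32.3 × 0.01 = 1.323, effective n 680/1.323 = 514 and power 80.9%. A whole number of 33 each gives 792, and 792 × 0.85/1.32 = 510, still above 506.

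**5. Sensitivity only; these inputs are assumptions.**
- With a t reference on 24 − 2 = 22 between-organisation degrees of freedom, power at 696 is 72.9% (design effect 1.28) or 74.3% (1.2365).
- For unequal organisation sizes the design effect is 1 + [(1 + CV²)m − 1] × ICC. With m = 24.65 and 22 degrees of freedom, CV 0.4 gives a design effect of 1.276 and power 73%; CV 0.8 gives 1.394 and 69%. The article gives no CV.

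**The case against.** The strongest reply is that the 80% is attached to the target of 763, rounded up to 800, and not to 696. If 800 people are recruited in 24 organisations, power on the plan's method is about 81%, so 24 organisations and 800 participants are compatible with the claim. The yield is given only as approximate, and the average of 72 comes from organisations signed up so far. This stands in part: it shows that the target is sound and that the fault lies in the cluster count or the yield. It does not remove the disagreement. Every employee is already invited and reminded, so more respondents must come from more organisations or a better response, and the article plans for neither.

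A second reply is that 29 might mean people who complete six months. On that reading 696/1.28 = 544, and power is 83.0%. But the article derives 29 from the survey response rate, takes attrition as a separate step, and applies the 29 to the total already inflated for attrition.

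A reader might also infer that true power is nearer 71 to 74%. The documents do not support that as a headline. It rests on a degrees-of-freedom method that the article does not name and may leave to the analysis plan, and on an assumed spread of organisation sizes. The size strata show that sizes may vary, not by how much.

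**Conclusion.** The point holds as an internal inconsistency. The stated clusters and yield deliver 696 employees, 9% below the stated minimum and 13% below the stated target. On the plan's own assumptions (difference 2, SD 8, ICC 0.01, 15% attrition, equal clusters), power is about 77%, or 78% with the post-attrition cluster size. The loss is modest, about 2 to 3.4 percentage points. The lower sensitivity values give a direction and a range, not an established figure.

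The power at 696 should not be read as the power of the primary analysis. Under Primary outcome, the article restricts that analysis to participants who receive MHFA, which it calls a small, non-random subsample. The calculation here, like the plan's own, concerns a comparison of all respondents.

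**What to change.** Restate Sample size {14} so that the number of organisations, expected respondents per organisation, total and power agree. Either of these would do:

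- Keep the clusters and yield: 24 organisations × 29 = 696 recruited, with power of about 77% for the all-respondent comparison on the stated assumptions.
- Keep 800, and state what it requires: about 33 respondents per organisation at 24 organisations (a 46% response, with a reason for expecting more than the pilot's 40%), or about 28 organisations (14 per arm) at 29 each.

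In either case, say that the figure is not the power of the per-protocol primary analysis. Add a labelled sensitivity for 22 between-organisation degrees of freedom (26 if there are 28 organisations) and for unequal sizes, using the CV of the organisations already signed up. The 28-organisation option should be checked in the same way: it gives 83% on the plan's method, but 78% with 26 degrees of freedom and an assumed CV of 0.65.

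The first option costs one rewritten paragraph and a slightly less favourable power statement. The second also costs either four more organisations or extra effort to raise the response.
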